#### Primary and secondary outcome analyses

Primary and secondary outcome measures will be used in the primary and secondary outcome analyses respectively. Vitalum's short-(week 47) and long-(week 73) term results will be analyzed with a 3-level multilevel mixed regression using Statistical Package for Social Sciences 15.0 (SPSS) and MLWiN. The three levels in the multilevel mixed regression were GPs, participants and measurements, given that participants are nested in GPs, and measurements (at baseline, 25, 47 and 73 weeks after baseline) are nested in participants. The quantitative dependent variables were the number of hours participants were moderately physically active per week, the number of days they engaged in moderate PA, the average daily intake of fruits, the average daily intake of vegetables, the number of days they consumed at least 2 pieces of fruit, the number of days participants consumed at least 200 g of vegetables, their total fat scores, BMIs, health-related quality of life and stage of change. The dichotomous dependent variables assessed whether participants met the public health guidelines measured with a combination of multiple items and one item, as described above. The independent variables were gender, education level, hypertension status, age, intervention group, behavioral determinants, whether they received a pedometer as a gift during the intervention period, batch number and region. Due to multiple testing, an alpha of .01 was used to evaluate results.

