### Study design

To ensure that we selected participants not satisfying the Dutch public health guidelines, people who returned the baseline questionnaire were included in Vitalum if they failed to meet at least two of these guidelines: PA and either fruit or vegetable consumption. Adequate saturated fat intake was not taken into account as an exclusion criterion, because most Dutch adults (90%) fail to meet the guideline for this behavior [66]. Saturated fat intake received less attention in Vitalum than PA and fruit and vegetable consumption for a practical reason – to reduce the length of the tailored letters and motivational interviews.

Participants were stratified based on hypertension status prior to randomization. In total, 1,629 (63%) of the 2,568 participants who filled out the baseline questionnaire were randomized in one of the four groups. A description of the study sample at baseline is shown in Table 1. Because data of the selected people (*n *= 6,420) were only available at group level, attrition analyses were executed at group level for age, gender and hypertension status. Participants in the sample (*N *= 1,629) were compared with those who had been excluded or refused to participate (i.e., non-participants; *n *= 4,791). These analyses revealed no significant differences in age between participants (*M *= 57.15, *SD *= 7.13) and non-participants (*M *= 57.02, *SD *= 7.38; *t*(6,418) = 0.62, *p *> .05), nor for gender, (*χ*^2^(1, *n *= 6,420) = 1.92, *p *> .05). However, participants (52% with and 48% without hypertension) were more likely to suffer from hypertension than were non-participants (49% with and 51% without hypertension; *χ*^2^(1, *n *= 6,420) = 4.53, *p *< .05).

**Table 1 T1:** Vitalum sample description (*N *= 1,629)

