### Statistical analyses

#### Sample size and power

The required sample size was determined using the formula for unpaired *t*-tests [114], as each effect test in a balanced 2 × 2 between-subject design (i.e., the TMI and the TPC main effects and their interaction) comes down to such *t*-tests (apart from having less residual variance). The sample size calculation was based on the following assumptions: (a) since results of similar studies were not available at the start of Vitalum, the sample size calculation was based on a small expected effect size (Cohen's d) of .3 [115]; (b) a power of .9; (c) an alpha of .01 to correct for multiple testing; (d) an intra class correlation of .02, where the correlation is based on random treatment by GP interaction (a random GP main effect does not affect the sample size in the event of person randomizations within GPs) [116]; and (e) an expected average number of participants per general practice of 70. Loss of power due to random dropout or a gain in power from including the pretest as a covariate in the analyses [117] was not taken into account in the sample size calculation. However, the loss of power due to 20% random dropout can be compensated by including the pretest as a covariate if it correlates .5 with the posttest – the latter correlation being a realistic assumption. These assumptions resulted in a required sample size at baseline of 1,600. Thus, Vitalum aims to assess 400 participants per group at baseline. Assuming 50% of people refuse participation, and 40% of the remaining group meet the recommendations for PA and nutrition and are thus excluded, at least 5,400 people must be invited to secure 1,600 for the study.

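### The power section offers the pretest as a covariate to offset dropout, but the analysis section makes baseline an outcome wave without stating equal group means; for PA-guideline adherence that wave is 0% by selection

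*Protocol article*

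**What the plan says.** Under Sample size and power, neither the loss from dropout nor the gain from a pretest covariate enters the calculation of 1,600. The section then says that "the loss of power due to 20% random dropout can be compensated by including the pretest as a covariate", provided that pretest and posttest correlate .5, which it calls realistic. No other provision for dropout is given there.

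Under Primary and secondary outcome analyses, the model has three levels, and "measurements (at baseline, 25, 47 and 73 weeks after baseline) are nested in participants". The independent variables listed are gender, education, hypertension status, age, intervention group, behavioral determinants, pedometer gift, batch and region. The pretest value of the outcome is not among them. Nor are time and group x time. The same section names guideline adherence on the combined measure as a set of dichotomous dependent variables.

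Under Study design, people were included if they "failed to meet at least two of these guidelines: PA and either fruit or vegetable consumption". Table 1 accordingly shows 0% meeting the combined PA guideline at baseline, against 11% for fruit and 7% for vegetables.

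**The concern.** A baseline value that sits in the outcome vector is not at the same time a covariate. The two sections therefore describe different analyses, and the protection offered in one is not visible in the other. Whether anything is lost depends on a choice that the text leaves open: whether the groups may have different baseline means. If they may, the treatment effect at week 47 is a difference in change. At a correlation of .5 that is no more precise than using the follow-up alone.

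A separate difficulty affects one primary outcome. If every participant is a non-adherer at baseline, a logistic model that includes the baseline wave has a baseline log-odds of minus infinity. Any odds ratio measured against baseline then has no finite value. Hypothesis 1 is worded as an increase from baseline, so an analyst could easily report such a contrast.

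**Working it through.** **Inputs, all from Sample size and power.** "The required sample size was determined using the formula for unpaired *t*-tests"; "a small expected effect size (Cohen's d) of .3"; power .9; "an alpha of .01 to correct for multiple testing"; "an intra class correlation of .02, where the correlation is based on random treatment by GP interaction"; "an expected average number of participants per general practice of 70"; 20% dropout; pretest-posttest correlation r = .5. Sidedness is not stated. Two-sided is assumed because it reproduces the stated figure and one-sided does not (1,380).

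**1. The article's own figure.** n per side = 2(2.576 + 1.282)² / 0.3² = 330.7, so 331, or 662 in total. The design effect is 1 + 69 × .02 = 2.38, and 662 × 2.38 = 1,576. The t-based n gives 1,585. Both agree with 1,600. At 1,600 without dropout the effective n per side is 800 / 2.38 = 336.1, z = 0.3 / √(2/336.1) = 3.889, and power = Φ(3.889 − 2.576) = 90.5%.

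**2. Variance factors for the week-47 effect at r = .5**, relative to the follow-up alone:
- pretest as covariate: 1 − r² = 0.75;
- baseline as outcome, group means free: 2(1 − r) = 1.00;
- baseline as outcome, group means constrained equal: 0.75.

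The two baseline-as-outcome factors were confirmed by generalized least squares with four occasions and compound symmetry.

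**3. Power after 20% dropout.** N = 1,280. Practice size either stays at 70 (design effect 2.38) or falls to 56 (1 + 55 × .02 = 2.10).

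| Model | Factor | 70 per practice | 56 per practice |
|---|---|---|---|
| Pretest as covariate, or equal baseline means | 0.75 | 92.5% | 95.6% |
| Baseline as outcome, free means | 1.00 | 81.7% | 87.0% |

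For example, free means at 70 per practice: 640 / 2.38 = 268.9 per side, z = 0.3 / √(2/268.9) = 3.479, and Φ(3.479 − 2.576) = 81.7%.

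The offset works on the first row: 1,280 / 0.75 = 1,707, which exceeds 1,600. On the second row it does not. Reaching 90% with 70 per practice would then take 1,576 / 0.8 = 1,970 to 1,600 / 0.8 = 2,000 participants. For r from .3 to .7 at 70 per practice, the covariate route gives 85.8% to 98.9% and the free-means change contrast 64.2% to 97.2%.

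**4. If only the listed group term is fitted.** Assume no effect at baseline and an effect of .30 at each of three follow-ups. The group coefficient averages four waves: 3/4 × .30 = .225. Under compound symmetry the variance factor of the four-wave mean is (1 + 3 × .5)/4 = 0.625. Then z = .225 / √(2 × 0.625 / 268.9) = 3.300 and power = 76.6%, about 77% (70 per practice).

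**5. PA-guideline adherence.** A random-intercept logistic model was fitted by maximum likelihood to simulated data: two groups of 400, three follow-ups and an all-zero baseline wave. The baseline intercept ran off to −10.5 and then, with more iterations, −21.0. The time terms ran the opposite way. The group log odds ratios at the follow-ups settled at 0.881, 0.685 and 0.868. These values and the log-likelihood equalled those of the model without the baseline wave.

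**The case against.** The strongest reply is that a baseline wave among the outcomes does not in itself lose precision. Randomization justifies equal baseline means, and with that constraint the gain is fully kept (factor 0.75). The list of independent variables also omits time, although separate short- and long-term results are promised, so the list is plainly not exhaustive. The full plan may include the pretest or the constraint. This stands: the loss is conditional, and a reader who infers that the plan certainly forfeits the gain goes further than the text allows. What does not go away is that the two sections as printed give the pretest different roles.

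The power section also says only that the loss can be compensated, and the 1,600 does not rest on the gain. That is right, but no other provision for dropout is offered there.

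The size can be argued down in three ways:
- A likelihood model keeps the baseline data of dropouts. With free means the variance relative to the full sample is then .75/.8 + .25 = 1.19 rather than 1.25, and power is 84.0%.
- If the covariate reduces only the residual part and not the practice component, the comparison at 56 per practice is 91.4% against 87.0%. The relevant sum is .02 × 56 + .98 × .75 = 1.855, in place of 2.10.
- The main-effect-only reading fits poorly with an analysis of weeks 47 and 73, so the 77% is a possibility and not a forecast.

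A reader might also infer that the PA-adherence model cannot be fitted at all. Step 5 shows otherwise. Only the baseline log-odds and contrasts against baseline are non-finite, and the analysis section names no such contrast as its target.

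**Conclusion.** The concern holds in conditional form. The two sections disagree on how the pretest enters. If baseline group means are left free, the offset for dropout is nil at r = .5. Power for the 2 x 2 contrasts is then about 82% (87% at 56 per practice) rather than about 92% (96%). This rests on a two-sided alpha, compound symmetry, dropouts contributing nothing, and a covariate that reduces variance in proportion at all levels. Relaxing the last two narrows the gap, but power with free means stays below the 90% target in each case computed at r = .5. With equal baseline means there is no loss.

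For combined PA-guideline adherence, the baseline wave adds no information on the follow-up contrasts. It leaves change-from-baseline odds ratios without a finite estimate and may stop the fit from converging. Fruit and vegetable adherence and the quantitative PA outcomes do not have this problem.

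The point is worth settling because the choice between these models, if left open, could be made after the data are seen.

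**What to change.** In Primary and secondary outcome analyses:
- Take only weeks 25, 47 and 73 as outcome measurements, include time and group x time, and enter each participant's baseline value of the outcome as a covariate. Where an outcome was not measured at week 25, use the follow-ups that exist.
- For quantitative outcomes, an equivalent alternative is to keep baseline as an outcome and state that group means at baseline are constrained equal.
- For PA-guideline adherence, leave baseline out of the outcome vector. Its pretest is constant at 0 and cannot serve as a covariate, so use baseline PA days and hours instead.

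The cost is a few sentences. Every baseline value needed is already collected, and the sample size does not change.

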#### Process evaluation

The telephone survey at week 25 and the first follow-up also contained process questions that addressed the quality of the intervention delivery. For TPC, these questions measured, for example, participants' overall satisfaction with the letter, whether they had received and read the letter, and whether the letter was personal, comprehensible and interesting. For TMI, the questions measured, for example, overall satisfaction with the interview, whether the interviewer listened to and understood the participant, whether there was sufficient time to ask questions, and whether the interview was interesting. The competence of the motivational interviewers in MI use was also assessed with the MITI 3.0 and 1-PASS as described above.

#### Cost-effectiveness analysis

A cost-effectiveness analysis of Vitalum will be executed if the interventions are found to affect the primary outcome measures [118]. The cost-effectiveness analysis, executed from a healthcare viewpoint, examines the costs and effects of intervention implementation. Direct medical costs involved in carrying out the intervention (e.g., printing and mailing letters for TPC, call charges for TMI) are measured [118]. Other healthcare consumption costs are expected to be equal between the groups and are therefore not part of the analysis. Because Vitalum's goal was to examine the intervention's effectiveness, the developmental costs of the intervention are considered sunk costs and not included in the cost-effectiveness analysis. This also holds for protocol-driven costs (i.e., costs of data gathered as part of a clinical trial [118]); for example, the cost of recording the motivational interviews or that associated with measuring control group participants' behavior and its determinants. Direct non-medical costs (e.g., traveling costs, which were not applicable to Vitalum) and indirect non-medical costs (e.g., productivity costs) are irrelevant given the healthcare perspective chosen.

Since Vitalum may affect both health behavior and health-related quality of life, cost-effectiveness analyses will focus on both levels. To measure cost-effectiveness on a behavioral level, Vitalum's primary outcome measures will be combined into two overall outcome measures: the percentage of improvement in a participant's health behaviors compared to baseline measured using multiple-item measurements; and the number of public health guidelines met by a participant according to the combined measure (0–3: PA, fruit consumption and vegetable consumption). Intervention costs per patient who improved at least 10% of one health behavior as well as costs per patient who reached a specific number of public health guidelines will be examined. For health-related quality of life, the average improvement in quality of life score (Quality Adjusted Life Years) will be assessed by the RAND 36-item Health Survey 1.0 [101,102], and intervention costs per patient related to health-related quality of life score will be examined.

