**Methods/Design:**

Dutch general medical practices (*N *= 23) were recruited via a registration network or by personal invitation. The participants were then enrolled through these general practices using an invitational letter. They (*n *= 2,881) received a written baseline questionnaire to assess health behaviors, and potential psychosocial and socio-demographic behavioral determinants. A power analysis indicated that 1,600 participants who were failing to meet the guidelines for physical activity and either fruit or vegetable consumption were needed. Eligible participants were stratified based on hypertension status and randomized into one of four intervention groups: tailored print communication, telephone motivational interviewing, combined, and control. The first two groups either received four letters or took part in four interviews, whereas the combined group received two letters and took part in two interviews in turns at 5, 13, 30 and 43 weeks after returning the baseline questionnaire. Each letter and interview focused on physical activity or nutrition behavior. The participants also took part in a telephone survey 25 weeks after baseline to gather new information for tailoring. There were two follow-up questionnaires, at 47 and 73 weeks after baseline, to measure short- and long-term effects. The control group received a tailored letter after the last posttest. The process, efficacy and cost-effectiveness of the interventions will be examined by means of multilevel mixed regression, cost-effectiveness analyses and process evaluation.

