Research into tailoring emphasizes the need to compare these methods with others concerning their effects on changing behavior [25,51]. The Vitalum study contributes to this need. Its design was inspired by the NC STRIDES Project, which compared the effects of computer tailoring to those of MI in a colon cancer prevention and control study on PA and fruit and vegetable consumption in participants aged 50 or older [52-54]. Vitalum examines the efficacy of computer tailoring and MI on PA, fruit and vegetable consumption and saturated fat intake in participants aged 45 to 70 with and without hypertension. We also assess Vitalum's efficacy for different education levels since health disparities between SES groups are increasing [55] and health behavior adoption varies between these groups [56,57].

Older adults are an important target group for research and the development of lifestyle interventions for several reasons. First, adults between 45 and 70 represent more than 20% of the population in European countries [58]. Second, this percentage is likely to increase in the coming years [59]. Third, most blood pressure-related deaths or nonfatal events occur in middle age or in the elderly providing a cue to action for this age group [8]. Finally, older adults are important targets for prevention because health improvements due to increased PA, fruit and vegetable consumption, and lowered saturated fat intake still contribute to reduced risk of morbidity and mortality rates in this group [1,7,60].

When Vitalum began in 2003 no results were available of studies that compared the economic consequences of interventions using computer tailoring and motivational interviewing. Physical inactivity, consuming too little fruit and vegetables and eating too much saturated fat may result in disease and loss of quality of life [8,61]. Therefore, Vitalum also aims to evaluate and compare the cost-effectiveness of computer tailoring and motivational interviewing.

This article describes the Vitalum study design, which may help others in developing of equivalent interventions.

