Vitalum's development was accompanied by practical and operational difficulties. First, although the recruitment of participants via GPs resulted in the required number of participants, this method was time consuming and difficult for both researchers and GPs. GPs had to invest time by providing participant data and excluding certain people; yet, since GPs prioritize patient care and cure and not research, recruitment took more time than planned. Second, the data had to be collected and treated in batches. Combined with the recruitment delay this meant that 18 months lapsed between the enrollment and baseline data collection of the first and last groups. Third, questionnaires with many items were needed to measure and target multiple behaviors and their determinants [25]. This may have increased chances of dropout and invalid data due to participants becoming annoyed [119]. Furthermore, although telephone surveys were planned to reduce dropout risk, they appeared too restrictive and more expensive than paper questionnaires. Thus, paper questionnaires were used to collect baseline and posttest data. To reduce dropout risk, however, we used telephone surveys (at 25 and 39 weeks after baseline) instead of paper questionnaires to gather new data for the computer tailoring interventions. Moreover, although sometimes recommended, we could not use relatively objective reference instruments such as biomarkers for fruit and vegetable consumption [99,120] to validate the self-report questionnaires because they were considered too time consuming and expensive [67,95]. We thus used validated self-report questionnaires only [97,99,100]. Also, participants were more likely to suffer from hypertension than non-participants. This may be caused by selection bias, in that people with hypertension are more willing to participate than those without. This was confirmed by the fact that people who completed the baseline questionnaire were also more likely to suffer from hypertension than people who were excluded or refused to participate. However, this bias may also have been increased by including participants who failed to meet at least two guidelines, since high blood pressure is associated with lack of physical activity and low fruit and vegetable consumption [8]. In addition, the cost-effectiveness analysis does not meet the criteria of a full economic evaluation from a societal perspective; but the cost-effectiveness outcome is not the primary goal of our study. Finally, participants in the TPC group received stage-matched advice based on the stages of change algorithm of the Transtheoretical Model [72]. Although the usefulness and validity of stage models in nutrition and PA research has been criticized [105,121,122], their use in tailoring is still regarded promising [123].

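### The cost-effectiveness comparison is a stated aim without condition, yet it is run only if an undefined efficacy finding is made first

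*Protocol article*

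**What the plan says.** The Background gives cost-effectiveness as an aim with no condition attached: "Vitalum also aims to evaluate and compare the cost-effectiveness of computer tailoring and motivational interviewing". The Methods/Design part of the abstract does the same: "The process, efficacy and cost-effectiveness of the interventions will be examined".

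The operative section, Cost-effectiveness analysis, is conditional: the analysis "will be executed if the interventions are found to affect the primary outcome measures". It names no outcome, treatment contrast or time point. The same section plans three kinds of effect measure: patients who improve by at least 10% on a behaviour, the number of guidelines met, and quality of life.

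Primary and secondary outcome analyses sets the general threshold: "Due to multiple testing, an alpha of .01 was used to evaluate results". The Discussion ranks the objective: "the cost-effectiveness outcome is not the primary goal of our study".

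**The concern.** A reader of the Background and abstract expects a TPC versus TMI cost-effectiveness comparison. A team that follows the operative section to the letter may not produce one. Three things follow.

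- **The aim can go unanswered.** Letters and telephone calls can differ in cost even if neither beats control, and a non-significant effect still has an estimate and an interval. The Discussion says that the results should help policymakers choose which approach to disseminate, and that choice needs the comparison either way.
- **Selection.** If the analysis is run only after a positive finding in the same participants, the behavioural effects that enter it tend to be overestimates, and the cost per unit of effect tends to look too low.
- **Mismatch and lack of definition.** The quality-of-life analysis is also gated on behavioural results, although quality of life is a separate secondary outcome. Because the trigger is not defined, whether it has been met could be settled after the results are known.

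**Working it through.** **Inputs from the protocol article**
- Sample size and power: "a small expected effect size (Cohen's d) of .3"; power .9; "an alpha of .01 to correct for multiple testing"; "an intra class correlation of .02" (treatment by practice); 70 participants per practice; 400 per group planned.
- Study design: 1,629 randomised, so 1,629/4 ≈ 407 per group.
- Hypothesis 1: a 10% rise over control, relative to the baseline mean, for TMI or TPC.
- Table 1, mean and SD: PA 4.7 and 3.8 hours/week; fruit 2.1 and 1.6 pieces/day; vegetables 165.2 and 82.4 g/day.

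**Assumptions.** The gate is two-sided p < .01, inferred from the general alpha. Table 1 SDs hold at follow-up. The design effect ranges from 1 to 2.38.

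**1. The plan's own figure.** n per side = 2(2.576 + 1.282)²/.3² = 331, or 662 in total. The design effect is 1 + 69 × .02 = 2.38, and 662 × 2.38 = 1,576. The stated 1,600 is reproduced to within 2%, so the sample size is not in question.

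**2. Gate at the planning effect (main effect, 800 v 800).** Effective n = 800/2.38 = 336 per side; SE = √(2/336) = .0771; d/SE = 3.89. P(pass) = Φ(3.89 − 2.576) = .905. The analysis is dropped 9.5% of the time. Mean estimate given significance, divided by truth = [3.89 + φ(2.576 − 3.89)/.905]/3.89 = 1.05.

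**3. Effects implied by Hypothesis 1**
- PA: .47/3.8 = .124
- Fruit: .21/1.6 = .131
- Vegetables: 16.52/82.4 = .200

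**4. Any-of-six gate.** The six tests are these three outcomes for TMI v control and TPC v control, at 407 per arm. I simulated them with the control arm shared and between-outcome correlation 0 or .3. The middle design effect takes two arms, so 35 per practice: 1 + 34 × .02 = 1.68.

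| Design effect | Gate passes | Analysis dropped | Mean inflation |
|---|---|---|---|
| 1 (no clustering) | 85–90% | 10–15% | 1.03–1.06 |
| 1.68 | 63–68% | 32–37% | 1.11–1.18 |
| 2.38 | 48–52% | 48–52% | 1.18–1.30 |

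**5. Single-outcome gate, one arm v control.** With 407 per arm and no clustering, SE = √(2/407) = .070. P(pass) = Φ(d/SE − 2.576) = .21 (PA), .24 (fruit), .61 (vegetables). The corresponding inflation is 1.78, 1.69 and 1.22. With a design effect of 2.38, P(pass) falls to about .08, .09 and .24.

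**The case against.** Several points on the other side have force.

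- **The condition is declared in advance.** An abstract and a background aim are summaries, and the operative section openly narrows them. The Discussion also says that cost-effectiveness is not the primary goal and that a full societal evaluation is not intended. This stands as to importance: the aim at risk is a secondary one. But secondary is not the same as conditional, and nothing in the Background or abstract tells the reader that the analysis may not be done.
- **The .01 trigger is an inference.** The Cost-effectiveness analysis section speaks only of an effect being found; the threshold comes from the outcome analyses section. This stands, and the calculation carries it as an assumption.
- **The size can be overstated.** From the single-outcome figures, a reader might infer that cost per unit of effect would be understated by about 44%, 41% and 18% (1 − 1/1.78, 1 − 1/1.69, 1 − 1/1.22). The documents do not support that. They do not fix a single-outcome gate, and they plan no cost ratio on mean PA hours, fruit pieces or vegetable grams. Quality of life is not a gating outcome and would inherit selection only through its correlation with behaviour.
- **Opening by chance.** A reader might also count nine primary measures × three active arms × two follow-ups = 54 tests and infer a false opening in up to 1 − .99^54 = 42% of null trials. That assumes an any-of-54 gate, which the documents do not state. It cannot be combined with drop rates from a single-outcome gate: the more tests that can open the gate, the less often the analysis is dropped and the smaller the inflation.

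**Conclusion.** The point holds in a limited form. An aim stated without condition meets an analysis that is conditional on an undefined finding, so following the plan exactly can leave a secondary aim unanswered and tends to feed favourable estimates into the analysis when it is run.

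The size depends on the reading. It runs from small (about 1 in 10 dropped, inflation about 1.05, at d = .3 for a main effect) to substantial (about a third to a half dropped, inflation 1.1–1.3, if Hypothesis 1 is exactly true, any of six tests opens the gate and clustering is as planned). A single-outcome gate would drop the analysis far more often.

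These figures rest on a two-sided .01 trigger, baseline SDs at follow-up and the assumed correlations. The inflation factors show direction and rough order only, because the planned cost-effectiveness measures are not the tested mean differences. The mismatch between aim and plan, and the undefined trigger, do not depend on any of these assumptions.

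**What to change.** Delete the condition in the Cost-effectiveness analysis section. Run the planned analysis for all groups whatever the efficacy result, including the quality-of-life part. Report incremental costs and effects against control and for TMI versus TPC, with their uncertainty; the choice of interval method can be left to the full analysis plan.

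The cost is a little more analysis work. Behaviour and quality of life are measured in the trial anyway, intervention costs are already to be measured, and the sample size does not change. With the condition gone, the analysis is always done and selection on significance no longer arises.
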